## A.5. Benefits to subjects and/or society

A.5.1. Describe how this study will contribute to generalizable knowledge that will benefit society.

Identification of infants with rare neurogenetic disorders at birth through Early Check (IRB #18-0009) affords us an unprecedented opportunity to intervene in ways that could improve developmental trajectories and quality of life for the children and their families. If the benefit of early, pre-symptomatic intervention could be demonstrated for these disorders, the findings would likely have significant generalizability to other conditions that result in intellectual and developmental disabilities, providing critical information to community-based early intervention programs about pre-symptomatic treatment in established conditions, and could expand perspectives regarding the benefit of including a broader range of conditions on the Recommended Uniform Screening Panel.

A.5.2. Does this study have the potential for direct benefit to individual subjects in this study?

Yes

*Consider the nature, magnitude, and likelihood of any direct benefit to subjects. If there is no direct benefit to the individual subject, say so here and in the consent form, if there is a consent form. Do not cite monetary payment or other compensation as a benefit.*

Explain

Infants involved in the study will receive intervention that addresses the core deficits seen in children with rare neurogenetic disorders (communication, social, sensory, cognition, motor skills) which may benefit them in the future progression of the condition. Additionally, children will gain access to early intervention pre-symptomatically or as very early symptoms emerge, which may be associated with improved developmental outcomes. The intervention will include parent education about the disorder as well as direct parent coaching around parent-child interactions and repeated comprehensive assessments of family and child functioning. This parent-mediated approach aims to achieve two goals (1) general enrichment of the core interactive social experience for infants and (2) specific attention within this to addressing any emerging atypical behaviors that might be expected at this age and their interactional consequence.

A.5.3. Are there plans to communicate the results of the research OR results of any clinical tests administered for the research back to the subjects?

Yes

If yes, describe

Parents will receive a brief summary report after each of the 6-36-month visits. This will include a summation of standard assessments typically used in clinical care, but presented to parents as findings from a research study and very clearly indicated as non-diagnostic.

Summary results of the larger study will be shared with families through a mailed letter after study completion.

## A.6. Risks and measures to minimize risks

*For each of the following categories of risk you will be asked to describe any items checked and what will be done to minimize the risks.*

A.6.1. Psychological

✓ Emotional distress

✗ Embarrassment

✓ Consequences of breach of confidentiality (Check and describe only once on this page)

✗ Other

#### A.6.2. Describe any potential psychological risks checked above and what will be done to minimize these risks

There are minimal anticipated risks to participating infants or families.

To minimize the risk of an infant becoming stressed, all assessment and intervention sessions will be conducted in a setting comfortable to the child. Intervention sessions will be conducted in the home. Assessments will be conducted in-home and in a laboratory setting that will be designed to be infant friendly, with appropriate furniture and toys. Parents of the infants will present during the assessments and infants will have access to them if they become distressed.

If an infant presents with an unusually fearful reaction and cannot be easily soothed or redirected, as decided by the interventionist/assessor or the parent, during the developmental assessments or the home intervention sessions the task will be discontinued and resumed only when the infant's behavior indicates an ability to participate without significant fear or frustration. If the infant seems unable to participate due to fear or frustration or the interventionist/assessor or the parent feels the task will be too stressful for the child, the assessment/intervention will be discontinued.

Only personnel who have completed the required human ethics trainings will have access to individuals private, identifiable information. All participants will receive a unique identification number (ID) that will be used for any documents, videos, and materials related to the child. Names associated with the ID will be kept in password-protected document on a secure computer server. All family/child paper and/or electronic data will be stored in a locked cabinet or in an encrypted computer. All video recorders will be stored in a locked cabinet. Videos will be removed and deleted from cameras and stored on a secure server in a timely manner. Materials in transit (i.e. videos, assessment protocols) will be kept in a locked box until securely stored on site. Any scientific reports, article submissions, or summaries of data will not include children/family names. Data will be presented in a summary format that will prevent any personal identification.

Because the LENA (used during PANDABox assessment) records not only the child's vocalizations, but also conversations or other background noise in the child's environment, it is possible that sensitive information may be recorded while the child is wearing the LENA device. Families will be given a data permission form that allows them to erase any section of the day or the whole recording before any additional coding is conducted. Participants are also clearly made aware of this risk in the consent form.

There is a slight risk that the heart rate monitor (used during the PANDABox assessment) will be uncomfortable to the participants. Research assistants will be well trained to help virtually guide parents in needed adjustments to improve comfort. Caregivers will also be assured that they can terminate any portion of the study, including collection of heart rate, at any time.

Reflecting on their infant's functioning during form completion may be distressing for parents. Although they may feel some distress with these activities, we do not anticipate it being any more distressing than what might be expected within the clinical setting.

Plans to ensure necessary intervention in emotional distress. Research team members will follow a protocol for emergency situations and the project will adhere to the state legal statutes governing mandated reporting of suspected child abuse. If, during any contact with a project staff member, a parent expresses suicidal ideation, or is so immobilized by symptoms that she or her child are in danger, or is in danger because of domestic violence, the research team member will assess the mother and contact Drs. [name], [name], or [name] (all licensed psychologists in NC). If the research team member is with the parent, they will remain with them until a safe resolution has been reached, (i.e., immediate referral to a community resource and/or involvement of supporters who can continue to ascertain the safety of the mother and infant/toddler after the team member leaves the premise).

Some infants may show early signs of developmental delay that warrant intervention. If an infant shows signs of developmental challenges, researchers will provide parents with information to follow up with their child's pediatrician for a referral to Part C Early Intervention programming.

There is a slim chance of a breach of confidentiality. RTI and UNC consider the privacy of research

participants to be of the upmost importance.

#### A.6.3. Social

- ☒ Loss of reputation or standing within the community
- ☒ Harms to a larger group or community beyond the subjects of the study (e.g., stigmatization)
- ☒ Consequences of breach of confidentiality (Check and describe only once on this page)
- ☒ Other

#### A.6.4. Describe any potential social risks checked above and what will be done to minimize these risks

No Answer Provided

#### A.6.5. Economic

- ☒ Loss of income
- ☒ Loss of employment or insurability
- ☒ Loss of professional standing or reputation
- ☒ Loss of standing within the community
- ☒ Consequences of breach of confidentiality (Check and describe only once on this page)
- ☒ Other

#### A.6.6. Describe any potential economic risks checked above and what will be done to minimize these risks.

There may be a possible loss of income due to participation in this project. While the research team will make an effort to accommodate family schedules in intervention sessions and assessments, there may be the rare circumstance where a working parent may need to miss work time not covered by leave or other means. To mitigate potential economic risk, participants will be compensated \$50 for each assessment visit.

#### A.6.7. Legal

- ☒ Disclosure of illegal activity
- ☒ Disclosure of negligence
- ☒ Consequences of breach of confidentiality (Check and describe only once on this page)
- ☒ Other

#### A.6.8. Describe any potential legal risks checked above and what will be done to minimize these risks

While participants and families will not be asked to disclose any illegal activity or negligence, research staff will spend a significant time interacting with families. Assigned interventionists will interact with families for at least 24 weeks for 1-2 hours per week through video calls and sessions in the home. Due to the length of interaction with families and the provision of services in the home, interventionists and assessors may become aware of such information. Project staff will be aware of their legal obligations to report any suspected cases of child abuse or neglect to the appropriate authorities.

#### A.6.9. Physical

- ☒ Medication side effects
- ☒ Pain
- ☒ Discomfort
- ☒ Injury
- ☒ To a nursing child or a fetus (either through mother or father)

A.6.10. Describe any potential physical risks checked above, including the category of likelihood and severity, and what will be done to minimize these risks. Where possible, describe the likelihood of the risks occurring, using the following terms:

- Very Common (approximate incidence > 50%)
- Common (approximate incidence > 25 - 50%)
- Likely (approximate incidence of > 10 - 25%)
- Infrequent (approximate incidence of > 1 - 10%)
- Rare (approximate incidence < 1%)

Describe severity of risks using the following grading scale:

- Mild- No disruption to the subject's ability to perform daily activities; may include non-prescription intervention only
- Moderate- Temporary interference with daily activities; may include prescription intervention
- Severe- Interference with daily activities; medically significant but not life threatening
- Life threatening

Examples:

Rare (< 1%) and Severe: blindness

Rare (< 1%) and Mild: dry skin, dry mouth, transient headache

If you are using these terms differently than described above, please provide your study-specific definitions.

Phase 1 trials: Due to limited experience, incidence may be better described as the number of events that have occurred in the total number of animals/humans studied.

Participants might feel discomfort while wearing the LENA vest and/or heart rate monitors. All efforts will be made to reduce discomfort; however, if participants don't reach a point of comfort during the assessment they will be allowed to remove the LENA vest and/or heart rate monitor at any time.

A.6.11. Unless already addressed above, describe procedures for referring subjects who are found, during the course of this study, to be in need of medical follow-up or psychological counseling

During Phase 1 of PIXI, the therapist will provide general education about the baby's disorder, support, and referrals for services as warranted by the family's expressed concerns.

A.6.12. Are there plans to withdraw or follow subjects (or partners of subjects) who become pregnant while enrolled in this study?

No

## A.7. Data and safety monitoring

A.7.1. When appropriate, describe the plan for monitoring the data to ensure the safety of participants. These plans could range from the investigator monitoring subject data for any safety concerns to a sponsor-based data and safety monitoring board or committee (DSMB, DSMC, DMC), depending on the study. For studies that do not raise obvious safety concerns, you may still describe your plans for monitoring the study as it progresses.

Although this study presents minimal anticipated risk, the study PI will be responsible for the safety of all participants and the validity and integrity of the data. The PIs will regularly monitor the study and data collection procedures and conduct team meetings to review the protocols for safety and confidentiality.

A.7.2. If not already addressed above, describe the plans for aggregate review of unanticipated problems (including but not limited to adverse events) across all sites, in order to monitor subject safety.

No Answer Provided

A.7.3. What are the criteria that will be used to withdraw an INDIVIDUAL SUBJECT from this study or halt the research intervention (e.g., abnormal lab tests, allergic reactions, failure or inability to comply with study procedures, etc.)?

While this study has no plans to withdraw individual subjects, if subjects are unable to attend intervention sessions or frequently cancel appointments participants may not be able to fully complete the intervention within the allotted time frame. If cancellations are frequent, a member of the study team will inform the participant of an intervention end date in order to accommodate further enrollment of participants. Subjects may voluntarily withdraw.

A.7.4. Are there criteria that will be used to stop the ENTIRE STUDY prematurely (e.g., safety, efficacy, unexpected adverse events, inability to recruit sufficient number of subjects, etc.)?

No

A.7.5. Will this study involve a data and safety monitoring board or committee?

No

## A.8. Data analysis

A.8.1. Summarize the statistical analysis strategy for each specific aim.

For this case series, analyses will be primarily descriptive. Researchers will first examine feasibility and acceptability and descriptive data on pre-post measures at the case level. Next, change scores on each measure over the intervention period will be reviewed to help identify primary outcome measures and effect sizes for a larger trial. Finally, the team will compare developmental and behavior profiles of this sample at age 3 to those of young children with the disorder who were not identified through Early Check (IRB #18-0009).

A.8.2. If this is a pilot study, please describe the future study and say how its study design, aims, sample size, and methods differ from the pilot study you are proposing.

Upon completion of the case series, the team will use data collected on family needs, acceptability and feasibility of the intervention, child skills, parent responsivity, and social validity to refine (1) PIXI and develop a formalized treatment manual for all components, (2) our hypotheses about treatment effects, and (3) our measurement plan. A meeting will be held with consultants and Early Check expert advisors during year 2 of this project to review results and plan next steps. It is anticipated revisions to include manualizing the content and strategies incorporated into parent calls, timing and telehealth revisions, possible adaptations to phase 2 necessary for unique needs of those with rare neurogenetic disorders, and development of fidelity measures for all components.

Although final decisions regarding next steps will be decided after completion of the case series, it is expected that the next stage of intervention development will be to implement the revised PIXI intervention in a preliminary efficacy wait-list control design trial. In this trial, the plan is for all families to begin phase 1 after diagnosis. Based on feedback from families, the addition of formal environmental enrichment components such as increased motor and language stimulation during phase 1 will be considered. Families will be randomly assigned to early phase 2 or delayed phase 2 (e.g., 3-month delay). After completion of all the components of PIXI, all families will return for posttest. The team anticipates measuring the same three areas as in the case series: child outcomes, parent responsivity, and social validity. Outcome measures will be completed and coded by a team who is blind to group assignment and to ongoing therapeutic conversations to reduce bias. Treatment fidelity of the manualized PIXI will also be measured.

A.8.3. Provide a compelling justification for the proposed sample size in terms of the likelihood of achieving each aim.

One of the challenges in designing an effective intervention for infants with rare neurogenetic disorders identified through Early Check (IRB #18-0009) is determining an appropriate comparison group for assessing efficacy of our intervention. Even with the most liberal of estimates of uptake for the Early Check program, we would still only anticipate identifying around 20 infants per year. Therefore, even in the best-case scenario, we would not have enough participants to power a true randomized control trial (RCT) of the intervention. To address this issue for the FX sample, we are proposing several activities, all of which are already underway.

First, we are currently working on a collaborative, multisite paper pooling early developmental data collected on young children with FXS. This paper will be based on the Mullen Scales of Early Development (Mullen), administered to over 300 children with FXS under the age of 5 (with an estimated 900+ assessment points) to provide an overview of the extent of delay in five core developmental areas (Cognition, Fine Motor, Gross Motor, Receptive Language, Expressive Language) for boys and girls with FXS under the age of 5. This data will provide a general estimate of functioning at discrete ages to serve as a comparison for those who are identified at birth with FXS and complete the PIXI.

Second, we will publish findings from a soon-to-be-launched survey on parent reports of early development and access to and dosages of early intervention services for a national sample of children under the age of 7 with FX. This will provide additional information about early experiences of young children with FX by which to compare the experiences of our Early Check sample.

And lastly, we will identify, through the RTI Our Fragile X World registry, as well as by working with North Carolina-specific FX advocacy groups (NC CSN and consultant [name]), a sample of children under 5 with FX who have lived in North Carolina for most of their lives ( $n = \sim 15$ ). We will recruit these children and their families into a study about early development of children with FX in North Carolina and will collect direct assessments of these children as well as parent perspectives on their child's access to and dosage of early intervention services in the state. Although this comparison cohort will still be limited by a historical confound, this sample will be our closest possible group to our Early Check (IRB #18-0009) sample.

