## Post Approval Submissions

### Modification Information

*To modify an approved study, edit the individual answers that make up the application. The questions below are intended solely for the IRB to have a summary statement of your requested action. The modifications cannot be processed until the actual changes have been made throughout the application.*

1. Provide a brief non-technical summary of any changes you will be making to the study (i.e., study application, project personnel, and/or study documents.) The text you enter here will be reproduced in the IRB approval document, and should contain the details that you and/or your sponsor find relevant (e.g., master protocol/amendment version number and date). Typical summaries are 50-100 words. PLEASE NOTE: THIS SECTION MAY BE EDITED BY THE IRB FOR CLARITY OR LENGTH.

The following changes are requested in this submission:

1. A participating family has asked that both parents be allowed to take part in the study. Allowing both parents to participate will likely improve the outcomes of the intervention, thus we would like to allow both parents to participate if both ask to participate. We will ask the 2nd parent to sign a 2nd consent form and ask them to complete the parent report surveys as well.

2. We are adding a virtual adaptation of the DAYC-2 (protocol has been uploaded) to offer participants more flexibility during telehealth appointments. We will be conducting the assessment with participants in addition to select components of PANDABox, and will only be administered if participants are not engaging in an in-person assessment, or completing the DP-4. Incorporating this measure will not add to the current battery but complement or supplement it accordingly. The addition of this measure will not alter the assessment times described in the current consent form. Because the time estimation is still accurate and the individual measures are not listed in the consent form, we do not plan to re-consent participants currently enrolled.

2. Is this study in Data Analysis only (i.e. enrollment, intervention and follow-up are complete)?

No

Total number of subjects enrolled to date:

30

Is this study currently open to the enrollment of new subjects?

Yes

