## A.2. Subjects

A.2.1. Total number of subjects proposed across all sites by all investigators (provide exact number; if unlimited, enter 9999):

120

A.2.2. Total number of subjects to be studied by investigators being provided oversight by the UNC IRB. (provide exact number; if unlimited, enter 9999):

120

A.2.3. If the above numbers include multiple groups, cohorts, or ranges or are dependent on unknown factors, or need any explanation, describe here:

The 120 participants above will typically be made up of parent-infant dyads (one parent and infant). However, if a second parent asks to participate, they may be enrolled as well and will be asked to participate in the same activities as the first parent.

A.2.4. Do you plan to enroll subjects from these vulnerable or select populations:  
If you will include children, prisoners or nonviable neonates or neonates of uncertain viability, please check the appropriate category below and complete the additional sections.

You should check "Pregnant women" if you specifically intend to recruit women who are pregnant or are not excluding pregnant women in biomedical research that is greater than minimal risk. Do not check if you are conducting a survey of the general public or conducting secondary data analysis or chart review not aimed at pregnant women.

Only check UNC-CH Student athletes, athletic teams, or coaches if you have specific plans to enroll these subjects. This is not applicable for intramural or club sports. For definitions and guidance see SOP 1201: Vulnerable subjects in research.

☒ Children (under the age of majority for their location)

Any minor subject who attains the age of majority during the course of the research study must provide consent as an adult, unless consent has been waived, which is requested in section D.3.1.

☒ Pregnant women

☒ Nonviable neonates or neonates of uncertain viability

☒ Prisoners, others involuntarily detained or incarcerated (this includes parolees held in treatment centers as a condition of their parole)

If an enrolled participant becomes incarcerated during the course of the research, they must be removed from the research project until such time as the IRB (and OHRP for NIH funded projects) approves the study to include prisoners, unless there is an immediate risk to the participant from ending treatments under the protocol.

☒ UNC-CH Student athletes, athletic teams, or coaches

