**This study will include an open trial of PIXI with a pre-post design. Below is a timeline for participants**

**from pre-enrollment through study completion.****Overall sequence for participants:**

1. Parents enroll in Early Check to permit newborn screening. Parents of infants who screen positive will be contacted and asked to permit confirmatory testing. When confirmatory testing confirms diagnosis, families will attend a genetic counseling session virtually or at the UNC Carolina Institute of Developmental Disabilities (CIDD) to receive this diagnosis and accompanying genetic counseling when the infant is approximately 2-3 months of age.
2. At this Genetic counseling visit, families will be informed about associated studies, including the present PIXI study. Parents who express interest in this study can enroll during this genetic counseling visit or take-home information about PIXI and contact the study team to enroll anytime during the infant's first 12 months of life. Families that wish to further contemplate enrollment in PIXI after their genetic counseling appointment will be called a week after their appointment to assess any further interest in the study. Parents of infants with FXPM diagnosed through Early Check will be invited to participate in PiXI when there are available slots. Eligible families will be provided with information about PIXI and if interested, added to the wait-list. Additionally, families with rare neurogenetic disorders who have not been identified through Early Check may self-refer to the study or be referred by a provider. These families who contact the study team and express interest in the study, will be provided the informational handout (attached). If families wish to enroll, they will be added to the waitlist and, when applicable, will schedule an appointment for their Baseline/Time 1 assessments. After enrollment in the study, the procedures for self-referrals and those identified through Early Check will be identical.

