Subjects will be recruited during the Early Check (IRB #18-0009) genetic counseling/confirmatory testing process. We will discuss with parents the intervention and provide them with a simple overview of the study. Parents who choose to defer enrollment will be called one week after their final genetic counseling visit and asked if they would like to participate. Additionally, families may self-refer to the study and contact the research team. If slots are available based on the age of their baby and the current number of infants receiving intervention, eligible self-referrals will receive an informational handout about PiXI (see attached). All families with infants diagnosed through Early Check will be invited to enroll in PIXI. Due to the limited number of interventionists, invitations to families with FXPM infants and self-referred families will be prioritized as slots become available according to the following priority list:

1. Infants with a confirmed diagnosis identified through Early Check (IRB #18-0009)
2. Infants with FXS whose families self-refer to the study
3. Infants with premutation fragile X (PMFX) identified through Early Check (IRB #18-0009) who show signs of delay at their 6-month assessment

4. Infants with PMFX identified through Early Check (IRB #18-0009) who don't show signs of delay at their 6-month assessment but may show increased signs of genetic risk or whose parents show increased anxiety regarding their child's development

If invited families choose to enroll, the research team will schedule a baseline assessment.

Even with the most liberal of estimates of uptake for the Early Check program, we would still only anticipate identifying around 10 eligible infants per year.

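### A.8.1 draws both the candidate primary outcomes and the effect sizes for the next trial from the same uncontrolled change scores, which do not estimate the contrast that trial is expected to randomise

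*Protocol*

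**What the plan says.** A.4.2 describes the study as an "open trial of PIXI with a pre-post design". There is no comparison group during the intervention period. A.8.1 opens with "For this case series, analyses will be primarily descriptive". It then says that "change scores on each measure over the intervention period will be reviewed to help identify primary outcome measures and effect sizes for a larger trial", and ends with a comparison at age 3 against children not found through Early Check.

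A.8.2 describes the trial expected to follow. There, "the plan is for all families to begin phase 1 after diagnosis", and "Families will be randomly assigned to early phase 2 or delayed phase 2 (e.g., 3-month delay"). Posttest comes once families have completed every component. The same section says that final decisions on next steps wait until the series is complete.

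A.8.3 adds external fragile X comparisons at discrete ages, plus a North Carolina cohort of about 15 children that it admits is limited by a historical confound.

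**The concern.** Two separate problems sit in one sentence of A.8.1.

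- **Selection and estimation from the same data.** When many measures are scanned and those that moved most are preferred, the chosen measure's observed change overstates its true change. Nothing in A.8.1 separates the choice of outcome from the estimate of its effect.
- **The wrong quantity.** Even for an outcome fixed in advance, single-group change in infants is not a treatment effect, and it is not the effect the next trial is expected to test. In that trial both arms receive Phase 1 and differ only in when Phase 2 starts.

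If such a figure became the target difference, the follow-on trial could look feasible when it is not. Supply is small: for Early Check, B.1.7 states that "we would still only anticipate identifying around 10 eligible infants per year". There is little room to absorb an optimistic planning value.

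**Working it through.** **Figures in the protocol.** The only size figure is 120 subjects (A.2.1), without alpha, power, SD or effect size, so there is no calculation to reproduce. A.2.3 says subjects are typically one parent and one infant, so 120 means at most about 60 infants. Modification Information gives 30 subjects enrolled to date, about 15 infants if all are pairs (an assumption). The measures table in A.4.2 lists about 27 entries, of which roughly 15 to 18 could give a change score across Times 1 to 3, before subscales are counted.

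**Part 1: selection, as an illustration.** Assume K = 15 measures, correlation ρ = 0.3, the same true standardised change δ = 0.2 on every measure, and choice of the largest observed change. None of these is stated in the protocol. With standard error 1/√n,

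expected largest change = δ + √(1 − ρ) × m / √n,

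where m = 1.736 is the expected maximum of 15 independent standard normals and √0.7 = 0.837.

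- n = 15: 0.2 + 0.837 × 1.736 / 3.873 = 0.2 + 0.375 = 0.575, about 0.57 SD.
- n = 60: 0.2 + 0.837 × 1.736 / 7.746 = 0.2 + 0.188 = 0.388, about 0.39 SD.

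Dividing by the sample SD instead of a known SD raises these to about 0.65 and 0.40 by simulation.

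If true changes differ, selection partly finds measures that really respond. With true changes spread evenly from −0.1 to 0.5, the excess of the chosen measure over its own true change falls to about 0.29 SD at n = 15 (from 0.375) and about 0.11 SD at n = 60 (from 0.19).

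**What this could do to a sample size.** Two-sample t-test, two-sided 5%, 80% power:

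| Planned on | Per arm | Power if the true difference is 0.2 |
|---|---|---|
| 0.57 | 50 | 17% |
| 0.39 | 105 | 30% |
| 0.2 | 394 | 80% |

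The table takes a pre-post change at face value as a between-arm difference. The two are on different scales: pre-post change here is in units of the SD of change, and conversion multiplies by √(2(1 − r)), where r is the within-child correlation. At r = 0.5 the factor is 1. At r = 0.8 it is √0.4 = 0.632, so 0.57 becomes 0.36. The protocol gives no r.

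For scale, the smallest detectable d with N infants in total is (1.96 + 0.84) × √(2 / (N/2)) by normal approximation: 0.89, 0.72 and 0.63 for N = 40, 60 and 80. Here 40 and 80 are 10 and 20 infants a year (B.1.7, A.8.3) over the 4 years in A.4.5, and 60 is the ceiling above.

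**Part 2: the contrast, which needs no assumed numbers.**

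- Pilot change over the intervention period = maturation + outside services + Phase 1 + Phase 2.
- Randomised difference expected in A.8.2 = the effect of starting Phase 2 earlier rather than later.

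Maturation, outside services and Phase 1 are common to both arms of the next trial and are not part of its contrast. The Phase 2 term differs too: the pilot compares after with before, whereas the next trial compares early with delayed. A.4.2 adds variation in exposure (4 to 12 Phase 1 calls, 6 to 20 Phase 2 sessions) and a change of Phase 2 programme after review of the first four participants.

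**Direction of bias.** For raw skill scores, growth pushes change upward. For age-normed scores such as the Vineland-3, change can go either way, since A.1.1 describes symptoms emerging in the first year.

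**Possible rescue.** The comparisons in A.8.1 and A.8.3 are at age 3 or at discrete ages. They do not control change over the intervention period.

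**The case against.** The strongest reply is that A.8.1 commits to less than it seems to. Change scores are only reviewed to help with the choice. Feasibility and acceptability are examined first, and A.8.2 refines the measurement plan using family needs, acceptability, social validity and an advisor meeting. A reader might infer that the measure with the largest change will become the primary outcome. No such rule is written, so the Part 1 figures are conditional.

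That illustration also takes equal true changes, which favours inflation, and the result depends heavily on n. This stands, and is why both ends of the infant range and the unequal-change case are shown.

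A reader might also infer that the next trial will be sized on the pilot change and so will be underpowered. The protocol does not say this. The next design is only expected, and A.8.3 already concedes that there are too few infants to power a true randomised trial. Low power would owe much to supply in any case.

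Nor can it be said that maturation always inflates the change. That fails for age-normed scores, and infant skill growth is not the mechanism for parent measures such as the PSI-4 or STAI.

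Finally, Time 2 falls between the phases, so a Phase 2 change can be computed. It is closer to the next trial's question, but it remains uncontrolled and is not an early-versus-delayed difference.

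What survives is the stated use: effect sizes for a larger trial are to come, at least in part, from uncontrolled change that also guides outcome choice. This is written in A.8.1, not a detail left to an analysis plan.

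**Conclusion.** The point holds in two parts of different strength.

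- **Firm:** change over the intervention period does not estimate the effect of early versus delayed Phase 2. This follows from A.4.2, A.8.1 and A.8.2 side by side, whatever the selection rule, provided the next trial keeps the expected design.
- **Conditional:** if measures are favoured for large change, the carried-forward effect is inflated. On the stated assumptions a true 0.2 SD appears as about 0.57 SD with 15 infants and 0.39 SD with 60. The inflation is smaller where true changes differ, and no exact figure can be derived from the protocol.

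The documents do not support the stronger conclusion that this series is invalid. Its analysis is descriptive and can be carried out as planned. The sentence should be fixed because informing a larger trial is what it is for, but the harm would fall on that later trial.

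**What to change.** Reword A.8.1 only:

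1. Choose candidate primary outcomes mainly on feasibility, completeness, reliability, floor and ceiling effects, and relevance, not on the size of observed change.
2. Replace the reference to effect sizes with planning quantities (SD, within-child correlation, attrition, missingness), each with a confidence interval. State that the next trial's target difference will be set from a minimum worthwhile difference for early versus delayed Phase 2.
3. Report Time 1 to Time 2 and Time 2 to Time 3 change separately, and state that neither is a treatment effect.

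The cost is a few sentences. No new assessment is needed, since Times 1 to 3 are already scheduled. Enrolment is still open (30 of 120 subjects), so the wording can be settled before most of the data exist. The downside is that the pilot change can no longer be quoted as an expected effect size.
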